### 2.3. HRV Parameters Measured

We will measure HRV parameters recommended by the ESC and the North American Society of Pacing and Electrophysiology guidelines [7]:

(1)Time domain parameters: standard deviation of all NN intervals (SDNN), HRV triangular index, the standard deviation of the average NN interval over short time divisions (SDANN), and the square root of the mean squared differences of consecutive NN intervals (RMSSD);(2)Frequency domain parameters: low-frequency power (LF), high-frequency power (HF), and LF/HF ratio.

Additionally, some nonlinear HRV parameters will be evaluated, such as SD1, SD2, SD2/SD1, approximate entropy, and sample entropy.

HRV will be measured in addition to medical and interventional therapy for myocardial infarction according to the latest ESC guidelines focused on STEMI [2]. HRV will be assessed using a medically approved wrist-wearable device (E4 wristband from Empatica, CE certified) for 5 min segments during myocardial revascularization by primary PCI (before and after revascularization). The E4 device will be placed on the non-dominant hand, with the case tightener on the top of the wrist. The validity of HRV measurement using an Empatica E4 wristband was previously confirmed in a clinical study [13]. Raw data regarding heart rate and HRV (interbeat interval data) will be extracted from the wristband and further analyzed using Kubios software. Among available E4 wristband sensors, photoplethysmography will be used to derive interbeat interval data from blood volume pulse analysis. The blood volume pulse signal has a sampling rate of 64 Hz (resolution 1/64 s) as specified by the manufacturer. All HRV parameters of interest (including frequency domain and nonlinear parameters) will be automatically calculated using Kubios software [18]. Moreover, eventual artifacts in raw data collection will be corrected using a very low threshold algorithm (0.45 s) in Kubios to avoid significant HRV parameters deformation. Additional HRV measurements will be performed after the index event (at one and six months).

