### 2.5. Outcomes and Follow-Up

The primary composite outcome will include all-cause mortality and major adverse cardiovascular events (MACE). MACE will include cardiac mortality, fatal and non-fatal myocardial infarction, unplanned target vessel revascularization (TVR), and stroke (ischemic or hemorrhagic).

In addition, several secondary outcomes will be analyzed: (a) all-cause and cardiac mortality; (b) fatal and non-fatal myocardial infarction; (c) unplanned target vessel revascularization; (d) target lesion revascularization (TLR); (e) stroke; (f) hospitalizations for heart failure; (g) ventricular arrhythmias; (h) LVEF and left ventricular diastolic function. Moreover, the primary composite outcome will be evaluated in a high-risk subgroup of patients, such as elderly patients or those with diabetes mellitus/chronic kidney disease.

TVR will be defined as new stenosis requiring PCI or CABG in another part of the coronary artery treated at the index event. TLR will include unplanned PCI or CABG for the same lesion revascularized during primary PCI. LVEF will be measured using two-dimensional transthoracic echocardiography (Simpson methods). At least E/A or E/e prime ratios will be calculated for left ventricular diastolic function. Ventricular arrhythmias will be defined as ventricular fibrillation or sustained ventricular tachycardia documented at electrocardiographic monitoring. The primary composite outcome and secondary outcomes will be evaluated during the hospital stay, at 1 month and 1 year following admission for STEMI. All data regarding the outcomes will be collected from secure medical records.

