### 2.6. Participation Timeline

The expected duration of the study is three years following ethical approval by the local ethical review committee. As a first step, eligibility criteria will be analyzed at patients’ admission to the catheterization laboratory. Patients will be enrolled if all inclusion criteria will be fulfilled. During primary PCI procedure, HRV will be continuously monitored using a wearable device, which will be further analyzed offline using Kubios software. Additionally, at the index procedure demographic data, time to primary PCI in relation to chest pain onset; data regarding comorbidities and cardiovascular risk factors; and specified clinical, biological, and echocardiographic parameters will be collected.

During the hospital stay, patients will be re-evaluated echocardiographically and pre-discharge LVEF will be recorded. All outcomes of interest will be reported at this first time point in order to analyze a possible correlation between previously measured HRV parameters and short-term adverse events.

At 1 month and at 12 months after the index event, HRV will be re-assessed. In addition, in these time frames, clinical and echocardiographic data will be collected. Primary and secondary outcomes will be reported and an eventual correlation with HRV measured during primary PCI, as well as after 1 month and 12 months, will be analyzed.

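### In-hospital VF/VT is counted from admission with no rule placing it after the HRV segment used as predictor, so early episodes can precede the post-revascularization HRV said to predict them

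*Protocol article*

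**What the plan says.** Section 2.5 sets one timetable for the primary composite and all secondary outcomes: "The primary composite outcome and secondary outcomes will be evaluated during the hospital stay, at 1 month and 1 year following admission for STEMI". Section 2.6 repeats it for the hospital stay and states the purpose: "All outcomes of interest will be reported at this first time point in order to analyze a possible correlation between previously measured HRV parameters". Table 1 marks secondary outcomes in hospital, at 1 month and at 12 months.

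The secondary list in Section 2.5 includes "f) hospitalizations for heart failure; (g) ventricular arrhythmias; (h) LVEF and left ventricular diastolic function". The arrhythmia outcome is defined thus: "Ventricular arrhythmias will be defined as ventricular fibrillation or sustained ventricular tachycardia documented at electrocardiographic monitoring". The definition has no start time and does not set aside episodes around the procedure. On the source of outcome data, the section says: "All data regarding the outcomes will be collected from secure medical records".

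For the predictor, Section 2.3 specifies recording "for 5 min segments during myocardial revascularization by primary PCI (before and after revascularization"), and Section 2.6 adds: "During primary PCI procedure, HRV will be continuously monitored using a wearable device". There are therefore at least two index measurements, one on each side of revascularization. Section 2.7 plans odds ratios, logistic regression and ROC curves relating HRV to the outcomes.

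**The concern.** A prognostic analysis needs the predictor to be complete before the event it is meant to predict. Here the predictor is measured during an acute procedure, and one of the outcomes, VF/VT, can occur before or during that procedure. If the event window opens at admission and the predictor is recorded later, some events come first.

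An association between VF/VT and HRV recorded afterwards can then run backwards: the arrhythmia, or what was done to treat it, may have changed the recorded intervals. The eligibility criteria in Section 2.2 already accept this mechanism, since they exclude several rhythm disturbances and certain drugs because they interfere with RR intervals and HRV. An odds ratio or c-statistic that includes such episodes would be reported as predictive performance although part of it is not prediction.

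The shared timetable also fits two outcomes loosely for other reasons. Heart failure hospitalization is scored during a stay in which the patient is already admitted, and post-discharge arrhythmia depends on monitoring that the schedule does not include.

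**Working it through.** The article states no figure on this point, so the check sets the timing statements side by side.

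**Step 1. When the outcome window opens.** Sections 2.5 and 2.6 and Table 1 score all outcomes over the hospital stay, which begins at admission. No sentence delays the start for any outcome.

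**Step 2. When the predictor is complete.** Section 2.3 gives a segment before and a segment after revascularization. Each is complete only when its 5 minutes have ended, and both end after admission.

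**Step 3. Order of VF/VT and each segment.**

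| VF/VT occurs | Counted in hospital as written | Order for pre-revascularization HRV | Order for post-revascularization HRV |
|---|---|---|---|
| A. After admission, before the pre-revascularization segment ends | Yes | Wrong | Wrong |
| B. After that, before the post-revascularization segment ends | Yes | Correct | Wrong |
| C. After the post-revascularization segment ends | Yes | Correct | Correct |

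For the post-revascularization segment the misordered events are A + B. For the pre-revascularization segment they are A only.

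**Step 4. Whether another rule restores the order.** Section 2.6 describes the HRV as measured earlier than the in-hospital events. This states an intention; it gives no rule on what to do with rows A and B. Section 2.7 contains no such rule either.

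**Step 5. Size.** Misordered events for the post-revascularization segment = N × (in-hospital VF/VT risk) × (share in A or B). The article gives N as at least 200. It gives neither of the other two terms, so no count follows from the documents.

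**Step 6. Heart failure hospitalization.** A patient in the index stay cannot be newly admitted, and Section 2.5 defines no separate in-hospital heart failure event. The in-hospital count is therefore 0 whatever N is, and no odds ratio or c-statistic can be estimated at that time point. The 1-month and 1-year results are not biased by this.

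**Step 7. VF/VT after discharge.** Table 1 schedules an ECG at 1 month and at 12 months and no continuous or ambulatory monitoring. Outcomes come from medical records. A post-discharge episode is thus captured if it was documented clinically or appears on a visit ECG. Capture is possible but not systematic.

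**The case against.** The strongest reply is that the article already intends the right order. Section 2.6 relates in-hospital events to HRV measured beforehand, the pre-revascularization segment precedes anything that happens during the intervention, and the reference to admission in Section 2.5 may serve only to date the 1-month and 1-year evaluations. Eligibility narrows the problem further: it is checked on arrival at the catheterization laboratory and requires sinus rhythm and signed consent, so some patients with VF/VT on arrival would not be enrolled. A condensed article may also leave event windows to a fuller document.

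Much of this stands. A reader might infer that arrhythmia during PCI always precedes the HRV meant to predict it. The documents do not support that, because row B is correctly ordered for the pre-revascularization segment. Eligibility does reduce row A. It does not empty it, since an episode that has resolved need not exclude the patient, and it does nothing about episodes during the procedure. Whatever the reference to admission dates, the hospital stay itself starts at admission. The appeal to a fuller document is weak because the article does not stay silent: it fixes a window for every outcome, and that window does not match the stated intention.

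A reader might also infer that post-discharge arrhythmia is not monitored at all, or that the 1-year arrhythmia result will largely repeat the in-hospital count. The first overlooks the scheduled ECGs and the medical records. The second needs event rates that the documents do not give. Removing the 1-year arrhythmia outcome would be a preference and is not a correction. A sudden death without a documented rhythm still counts in all-cause mortality and so in the primary composite; the article does not say how it is coded for the arrhythmia outcome.

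**Conclusion.** The point holds for the time order of VF/VT and index HRV. As written, episodes after admission and before the end of the post-revascularization segment are in-hospital outcomes analyzed against HRV recorded after them. The same applies to the pre-revascularization segment only for episodes before that segment ends.

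The number of events involved cannot be derived. Any figure would be the product of an assumed VF/VT risk and an assumed timing. That the bias is material rests on two assumptions: that some enrolled patients have such early episodes, and that an episode or its treatment alters HRV recorded soon afterwards. VF/VT is a secondary outcome and not a component of the primary composite, so the primary result is not affected by this route.

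The empty in-hospital cell for heart failure hospitalization is certain but biases no estimate. The post-discharge arrhythmia issue concerns how the result is described. Both are minor.

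**What to change.** In Sections 2.5 and 2.6, state that for each index HRV segment only events after the end of that segment count as outcomes, and that VF/VT before that time is reported as a baseline characteristic. This needs the clock times of the segments and of any early VF/VT. The downside is fewer countable in-hospital arrhythmia events, with the larger loss for the post-revascularization segment.

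As minor wording in Section 2.5:

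- Count heart failure hospitalization from index discharge and report it at 1 month and 1 year only.
- Describe post-discharge VF/VT as clinically documented, with no scheduled continuous monitoring.

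Neither change requires an extra visit or procedure.

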### 2.7. Statistical Analysis

SPSS statistical software version 26.0 will be used (IBM SPSS Statistics, New York, NY, USA). Descriptive statistics will be applied to characterize enrolled patients. Normally distributed data will be represented as mean and standard deviation, while non-normal distributed data will be displayed as median and Inter Quartile Range (IQR). Also, relevant graphics will be used when possible. 

When appropriate, data will be analyzed using parametric (Student’s *t*-test) and non-parametric tests (Mann–Whitney–Wilcoxon). In addition, for statistical hypothesis testing, Student’s *t*-test will be applied in case of continuous variables, while categorical variables will be compared using the chi-square test. Missing data will be handled using a multiple imputation approach.

Odds ratio (OR), corresponding 95% confidence intervals, and p-values will be calculated for each variable related to investigated outcomes. A *p*-value < 0.05 will be considered statistically significant. Univariate logistic regression models will reveal statistically significant variables associated with pre-specified outcomes. Afterward, variables documented as statistically significant in univariate logistic regression models will be included in multivariate analysis. Moreover, the prediction accuracy of time and frequency domain HRV parameters for primary and secondary outcomes will be evaluated using the Receiver Operator Characteristics (ROC) curve. The sensibility, specificity, and c-statistic of individual HRV parameters will be calculated. Additionally, the Kaplan–Meier survival curve will be used to analyze time to event variables.

In addition, the role of HRV parameters for adverse outcomes prediction will be analyzed in three subgroups of high-risk patients, including patients with chronic kidney disease, diabetes mellitus, and elderly participants.

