## Figures and Tables

**Table 1 sensors-22-03571-t001:** Collecting data at specific time points.

Procedures/Timepoint	Study Interventions				
	Enrollment	Baseline	During Hospital Stay	1 Month	12 Months
**Enrollment**	X				
Screen for eligibility	X				
Contact information	X				
Informed consent					

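### Medical records are the only stated outcome source, and no step establishes vital status for patients who miss the 1- or 12-month visit, although all-cause death is in the primary composite

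*Protocol article*

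**What the plan says.** Section 2.5 puts all-cause mortality and MACE in the primary composite and sets the assessment times: "The primary composite outcome and secondary outcomes will be evaluated during the hospital stay, at 1 month and 1 year following admission for STEMI". It then names the data source without exception: "All data regarding the outcomes will be collected from secure medical records".

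Section 2.6 adds contact with patients after discharge: "At 1 month and at 12 months after the index event, HRV will be re-assessed", and "in these time frames, clinical and echocardiographic data will be collected". Table 1 agrees. It marks ECG, echocardiography, HRV, clinical data and both sets of outcomes at 1 and 12 months. It also lists "Contact information" at enrolment, but no section gives that item a part in finding outcomes.

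On missing values, section 2.7 has one general sentence: "Missing data will be handled using a multiple imputation approach". The same section plans Kaplan–Meier curves for time-to-event variables.

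For secondary outcome (g), section 2.5 says: "Ventricular arrhythmias will be defined as ventricular fibrillation or sustained ventricular tachycardia documented at electrocardiographic monitoring". After discharge, Table 1 schedules an ECG at each of the two visits and no ambulatory or continuous monitoring.

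**The concern.** Death is the one component of the primary outcome that a patient cannot report at a visit. Someone who dies at home may leave no medical record that the investigators see, and in the study data looks like any other patient who did not come back. If the reason for the missing outcome is the outcome itself, imputing from patients whose status is known breaks the missing-at-random assumption on which multiple imputation usually rests.

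Objective 2 in section 2.1 is the relation of HRV to short- and long-term events. If unrecorded deaths are more common at low HRV, the main association is pulled toward no effect. If they are unrelated to HRV, the cost is mainly events and power, in a study of at least 200 patients.

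Ventricular arrhythmia has a related problem. One definition serves three time points, but the chance of detection differs: patients may be monitored in hospital, whereas afterwards only two visit ECGs are scheduled. Later events will be documented mainly in patients who come back to hospital and are monitored there.

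**Working it through.** **What the stated steps would capture after discharge**

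| Patient | Route to the outcome in the article | Captured? |
|---|---|---|
| Attends; event treated at the study hospital | Records and visit | Yes |
| Attends; non-fatal event treated elsewhere | Clinical data at the visit | Can be |
| Does not attend; dies in a hospital whose records are consulted | Records | Yes |
| Does not attend; dies out of hospital | None stated | Can be missed |
| Does not attend; alive | None stated | Cannot be told from the row above |

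The gap is confined to non-attenders. The article gives no expected number of them.

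**Size.** The article states no event rate, effect size, power or drop-out, so there is no figure to reproduce. Only the 200 patients (section 2) and the 0.05 significance level (section 2.7; two-sided assumed) come from it. Everything else below is assumed.

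*Calculation A: two halves of 100 patients, true risk ratio 2.* With overall risk P, the high-HRV half has risk 2P/3 and the low-HRV half 4P/3. For P = 10% these are 0.0667 and 0.1333.

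- Full capture: 20 events. OR = (0.1333/0.8667) / (0.0667/0.9333) = 0.1538/0.0714 = 2.15. Power 0.35.
- 30% missed in both halves: risks 0.0933 and 0.0467, 14 events. OR = 0.1029/0.0490 = 2.10. Power 0.25.
- 30% missed in the low half only: risks 0.0933 and 0.0667, 16 events. OR = 0.1029/0.0714 = 1.44. Power 0.10.

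Range over P, with 30% missed:

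| P | True OR | OR, even loss | OR, loss in low half only | Power: full / even / low only |
|---|---|---|---|---|
| 5% | 2.07 | 2.05 | 1.42 | 0.19 / 0.14 / 0.07 |
| 10% | 2.15 | 2.10 | 1.44 | 0.35 / 0.25 / 0.10 |
| 15% | 2.25 | 2.16 | 1.47 | 0.51 / 0.36 / 0.14 |
| 20% | 2.36 | 2.23 | 1.49 | 0.66 / 0.48 / 0.18 |

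With 10% missed instead, at P = 10%, the OR is 2.14 (even) or 1.91 (low half only).

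*Calculation B: continuous HRV.* Standard-normal HRV, logit slope −0.6 per SD (OR = e^−0.6 = 0.55), 12% events. Events are removed at different rates below and above the median, and the logistic model is refitted:

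| Missed below / above median | Share of all events lost | Recorded rate | OR per SD |
|---|---|---|---|
| 0 / 0 | 0 | 12.0% | 0.55 |
| 20% / 20% | 20% | 9.6% | 0.56 |
| 15% / 10% | 13.5% | 10.4% | 0.57 |
| 30% / 10% | 24% | 9.1% | 0.63 |
| 40% / 10% | 31% | 8.3% | 0.67 |

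Both calculations show the same pattern. Even loss leaves the odds ratio almost unchanged and costs events and power. HRV-related loss attenuates it, and by a material amount only when the loss is large and clearly uneven.

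**Arrhythmia.** No arithmetic applies. Section 2.5 requires documentation on monitoring at all three time points, while Table 1 offers only visit ECGs after discharge. The article does not say whether the 1-month and 1-year counts include in-hospital events.

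**The case against.** The other side has real weight. Follow-up is not passive: every patient is expected at 1 and 12 months, a survivor treated elsewhere can say so, and a missed visit may itself prompt tracing. Medical records are not limited in the text to the study hospital. Collecting contact details suggests that contact was intended. This is also a condensed article, and tracing procedures are often left to the full protocol.

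Most of that stands, and it confines the problem to non-attenders. It does not remove it. The article is not simply silent: it fixes one source for all outcome data. A visit cannot reveal the death of someone who does not attend, and a home death may generate no record under any reading of the phrase.

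Three stronger readings are tempting but unsupported:

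- A reader might infer that out-of-hospital deaths will be missed. They can be; the article does not show that they will.
- A reader might infer that having no record counts as being event-free, or that deaths will be imputed. Nothing says the first. The second is only left open by a general imputation sentence that does not mention outcomes; in the planned Kaplan–Meier analysis a non-attender would ordinarily be censored.
- A reader might infer that 1-year arrhythmia is in-hospital arrhythmia under another name. That would need cumulative counting, which is not stated, and events documented on monitoring at readmission would also count.

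The loss rates are assumed, and mild uneven loss barely moves the estimate. With 200 patients and the assumptions of calculation B, sampling alone spreads the estimated odds ratio from about 0.33 to 0.80, wider than the shifts shown. That limits any claim about size, but a systematic loss of deaths is still worth preventing when prevention is cheap.

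**Conclusion.** The point holds in a limited form. As written, the plan has no stated way to learn whether a non-attender has died, although death from any cause is in the primary composite to 1 year, and its general imputation rule does not exempt outcomes. If the resulting loss is related to HRV, the primary association is biased; if the loss is even, the harm is mainly fewer events and less power. That low-HRV patients are over-represented among missed deaths is plausible but not shown. The figures above illustrate the mechanism and are not an estimate for this study.

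For ventricular arrhythmia, detection is unequal before and after discharge and the later counts are not defined. This calls for separate reporting and clear labels. It does not require dropping the 1-month and 1-year results.

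**What to change.** In section 2.5:

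- Add to medical records a check of vital status and primary-outcome events at 1 and 12 months for every patient, or at minimum for every non-attender. Do this by telephone to the patient or relatives, using the contact details already collected, and by the civil death record where permitted.
- State that absence of a record is not taken as event-free.
- Report ventricular arrhythmias during the monitored index stay separately from those after discharge, and label the latter as clinically detected (arrest, death or admission).

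In section 2.7:

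- Exempt death from multiple imputation.
- Censor patients who cannot be traced at last contact in the Kaplan–Meier analysis.

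Cost: up to 200 × 2 = 400 short calls at the minimum sample size, fewer if only non-attenders are called, plus a few sentences of text. No planned outcome is given up.
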